### Adoption

The study will evaluate the proportion of schools, youth centers, and therapists willing to participate, providing insights into broader program acceptance and feasibility.

### Implementation

We will examine the effectiveness of data collection and participant engagement on Instagram, which is critical for understanding how the program can be successfully implemented in a larger trial.

### Maintenance

A 6-month follow-up will gauge the long-term impact of the intervention on intended outcomes and evaluate interaction and retention rates. These data are crucial for understanding the sustainability of the program’s effects.

The operationalization of these dimensions is summarized in Table 2. The trial will be conducted in a single-group design.

**Table 2 table2:** Overview of the questionnaires used with a single-group design to assess primary and secondary outcomes in preintervention, postintervention, and 6-month follow-up surveys.

Outcome and construct					Questionnaire		Reliability
**Primary outcomes**							
	**Life skills**						
		Decision-making or goal setting		Subscale “goal setting” of the Life Skills Ability Scale (LSAS) [73]		α=.89	
		Problem-solving		Subscale “problem solving” of the Life Skills Ability Scale (LSAS) [73]		α=.85	
		Creative and critical thinking		Self-generated items to test knowledge based on the developed program content		—^a^	
		Communication		Subscale “communication” of the Life Skills Ability Scale (LSAS) [73]		α=.78	

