### Reach

The focal point of our study is to encompass a broad and representative demographic of 9th- and 10th-grade adolescents. To achieve this, we are targeting a diverse population from various school types, including grammar schools, comprehensive schools, secondary schools, and independent schools. Moreover, recognizing the importance of reaching adolescents undergoing high stress, recruitment efforts are also extended to youth centers and therapeutic facilities. We will explore the characteristics of adolescents who have consented to participate. Based on insights from the pilot study, we anticipate varying levels of engagement among the participants: some may actively engage with the program’s social media content, while others may have minimal to no interaction although initially interested. This variance allows for a quasi-experimental design, using engagement levels (ranging from none to high) as the basis for group assignment. Such a design is capable of highlighting differences between these engagement groups, and we will explore the predictors that are associated with active engagement or no or low engagement. We will also conduct a qualitative process evaluation to explore the facilitators and barriers encountered during recruitment. This will involve the recruitment team documenting feedback about the program and information event, as well as the reasons participants choose to join or decline participation. This documentation will be captured both in written form and verbally.

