### Effectiveness

The program’s effectiveness will be evaluated by its impact on life skills, social media–related skills, health status, risk behaviors, and school performance. Using the quasi-experimental design, we aim to test the hypothesis that enhancing digital life skills through the intervention leads to improved social media skills and reduced risk behaviors. To detect medium-sized effects, a power analysis indicates the need for 128 adolescent participants (power=0.8, α=.05), aligning with existing evidence of medium effect sizes in digital interventions (d=0.30 to 0.76) [72]. This evaluation will provide crucial data for potential effectiveness, shaping the direction of future trials.

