### Data Collection

In this study, both qualitative and quantitative data are gathered to explore the RE-AIM framework’s dimensions, involving (1) documentation by the recruitment team and (2) personal-level outcomes via questionnaires. Figure 1 illustrates the study design with the recruitment phase and points of assessment.

To assess RE-AIM’s aspects of reach, acceptance, and implementation, data will be collected on the number of schools, youth centers, and therapeutic facilities contacted per state; their response rates; information events held; and consents after the event. The recruitment team will also document institutions’ responses.

Personal level characteristics outcomes, measuring reach, effectiveness, and maintenance, are gathered through web-based questionnaires in a preintervention, postintervention, and follow-up design. Participants and institutions receive unique codes for tracking. The institutional link aims for support through teachers or youth workers and therapists and thus comprehensive data collection by conducting the entire study, including data collection, within 1 school year. Schools optionally receive supplementary teaching materials for the leduin program content.

The following constructs are collected by means of questionnaires: primary outcomes (life skills [decision-making or goal setting, problem-solving, creative and critical thinking, communication, interpersonal skills and empathy, self-confidence and self-efficacy, managing emotions, and managing stress], and social media–related skills [media-based empathy, cyberbullying, smartphone, and addictive or disordered social media use]); secondary outcomes (health status [well-being, subjective health and mental health, and life satisfaction], risk behavior [substance use], and school performance); and covariants (acceptance and feasibility of the program and sociodemographic variables). Table 2 lists the survey instruments used to measure the constructs just described, including reliability.

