### Data Analysis

#### Statistical Methods

Quantitative analyses will vary according to the different dimensions of the RE-AIM framework [71]. The software R Studio (Posit) and SPSS (IBM Corp) will be used [95]. Multilevel logistic regressions will be conducted to evaluate the dimensions of reach, acceptance, and implementation. Here, the extent to which the following variables influence institutions’ initial interest in the program, individuals’ initial willingness to participate in the program, completeness of data, and individual engagement within the program is examined: socioeconomic status, gender, age, mode of recruitment (school, youth center, and therapeutic facility), school type, performance, well-being, life satisfaction, and mental health. The initial interest of institutions in the program is operationalized by the proportion of institutions (schools, youth centers, and therapeutic institutions) that participated in an information session. The initial willingness of individuals to participate in the program is assessed by the percentage of students who decide to participate in the program after an information session. The completeness of data is examined by the percentage of data in the preintervention, postintervention, and follow-up surveys, and individual engagement is measured by the participants’ self-assessment.

For quantitative analyses of the dimensions of reach, effectiveness, and sustainability, mixed-effect multilevel regression analysis with institutions (school, youth center, and therapeutic facility), classes, and individuals as evaluation levels and 3 measurement points (preintervention, postintervention, and follow-up) will be carried out. The multilevel structure will be assumed if the actual design effect resulting from the intraclass correlation is >2 [96]. The influence of covariants such as gender, age, and socioeconomic status will be controlled. In addition, the individual courses in the outcome variables, as described before, will be examined by using latent growth models across the 3 time points. Logistic regressions will be conducted to investigate the impact of the program on participants’ addictive or disordered social media use by comparing pre- and postintervention data.

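### Creative and critical thinking is a primary life-skill outcome, but its only instrument is a self-made test of program knowledge, so retained content can be reported as a skill gain

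*Protocol article*

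**What the plan says.** Table 2, under primary outcomes and life skills, gives one instrument for creative and critical thinking: "Self-generated items to test knowledge based on the developed program content". The reliability column is marked as not applicable. The Data Collection section confirms the tier: "primary outcomes (life skills [decision-making or goal setting, problem-solving, creative and critical thinking" and so on through eight life-skill constructs. The other seven each have at least one cited questionnaire with a reliability value. No other measure of creative or critical thinking appears in Table 2.

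On design, the Maintenance section states: "The trial will be conducted in a single-group design". The Reach section describes the internal comparison as "using engagement levels (ranging from none to high) as the basis for group assignment". Statistical Methods plans multilevel regression over "3 measurement points (preintervention, postintervention, and follow-up) will be carried out", adjusted for covariates such as gender, age and socioeconomic status. The Effectiveness section gives life skills a causal role: "we aim to test the hypothesis that enhancing digital life skills through the intervention leads to improved social media skills and reduced risk behaviors".

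The Limitations section covers sampling bias, confounding of engagement with outcomes, dropout, reliance on Instagram, length of follow-up and effect size. It does not mention that one primary measure is built from the program's own content.

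**The concern.** The outcome carries the name of a skill, while the instrument is described as a knowledge test on the material that the intervention delivers. A knowledge test shows whether content was taken in. It does not show, without further evidence, that adolescents think more critically or creatively.

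The design makes this matter more. There is no group that takes the same test without being offered the content. The nearest substitute is the low-engagement group, and low engagement means having seen less of what is tested. A gain, or a gradient with engagement, in this outcome would be reported under primary life skills. It could then be read as support for the hypothesis that the program enhances life skills, and carried into the cluster-randomized trial that the abstract foresees. Randomization there would not cure the problem if the same items were reused, because controls would not have seen the content.

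**Working it through.** **The plan's own figure.** The Effectiveness section says "a power analysis indicates the need for 128 adolescent participants (power=0.8, α=.05" for medium-sized effects. Assuming d=0.5, a two-sided test and two equal groups, the normal approximation gives n per group = 2(1.960 + 0.842)²/0.5² = 62.8, so 63 per group and 126 in total. The exact two-sample t-test gives 63.77, so 64 per group and 128 in total, with power 0.801. The figure reproduces. The present point is about what is measured and does not depend on it.

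**What the comparisons can identify.** Write the score on these items as Y = a·K + b·S + error, where K is knowledge of program content and S is creative and critical thinking skill.

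- Pre to post: E(ΔY) = a·ΔK + b·ΔS.
- High versus low engagement: E(ΔY high − ΔY low) = a·(ΔK high − ΔK low) + b·(ΔS high − ΔS low).

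Each comparison yields one observed quantity for two unknown terms. With ΔS = 0 throughout, both are still non-zero whenever a > 0 and content is retained, more so by those who engaged more. The planned covariates do not separate the terms, because the difference in K comes from exposure to the content, which is what engagement represents. An independent measure of S would separate them, and Table 2 has none.

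**Illustration with assumed effects.** Suppose skill is unchanged and only knowledge moves, by a standardized amount d. No value of d for these items is given in the article. The range below uses the ends of the effect range cited for digital interventions (0.30 and 0.76), the medium value 0.5, and a smaller 0.2. Two-sided 5% tests, with clustering and dropout ignored:

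| Assumed knowledge effect d | 64 vs 64 by engagement | Pre–post, n=128, correlation 0.5 |
|---|---|---|
| 0.2 | 20% | 61% |
| 0.3 | 39% | 92% |
| 0.5 | 80% | over 99% |
| 0.76 | 99% | over 99% |

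The pre–post column uses d/√(2(1 − r)); with r=0.5 the divisor is 1. With r=0.7 the first two entries become 83% and 99%. The table gives the chance that a knowledge effect of that size would be significant under the label creative and critical thinking. It does not show that such an effect exists.

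**Extent.** The Data Collection section lists eight life-skill constructs and four social media–related ones as primary. This point affects one of the eight, or one of the twelve.

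**The case against.** The strongest reply is that the items are not shown. The article calls them knowledge items but does not say that they test recall. One module covers information, and the introduction ties social media literacy to critical thinking. Some items might ask adolescents to apply what they know, for example by judging a post. The article also condenses a fuller protocol. This stands as a limit: a reader might infer that exposure must show up as a skill gain, and the documents support only that it can.

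Second, engagement is self-assessed, so it is a noisy proxy for content seen. A reader might infer a bias that always favours the program and grows steadily with engagement. Retention would push scores in that direction, but a steady gradient is an assumption.

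Third, no composite life-skills score is defined, and no rule makes one positive construct a positive primary result. The other life-skill scales are unaffected.

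Fourth, the stakes are limited. Reach is the main aim, effectiveness is presented as a first indication, and the missing control group and confounding by engagement are acknowledged. This lowers the weight of the point but does not answer it: those admissions concern who engages and with whom they are compared, not whether the instrument measures the named construct.

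Two further complaints would be weak. New items have no published reliability, and the table says so openly; several other rows also lack a value. Giving the items before the program describes any pretest.

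**Conclusion.** The mismatch is real and rests on what the article states: a skill in the primary tier, measured only by items described as a knowledge test on program content. Followed as written, the plan could report a gain in program knowledge as a primary gain in creative and critical thinking, and neither of its comparisons could reveal the error.

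The size is unknown. It depends on item wording that is not shown and on how much content is retained. It is tempting to read one in eight, 12.5%, as a magnitude, but that is a count of constructs and not a weight in any result. The percentages in the table above rest on assumed effects, equal groups and an assumed pre–post correlation. The documents do not support a claim that the primary life-skills result as a whole is undermined. The point should be fixed, but it is confined to one construct.

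**What to change.** Keep the items and relabel them as program knowledge. Move them from the primary life-skills outcomes to a secondary or process outcome, and draw no conclusion about creative or critical thinking from them. Date the change, and make it before these items are analyzed.

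The edits fall in three places: the row in Table 2, the list of primary outcomes under Data Collection, and the matching row of Table 3. If the items become a process outcome, the Implementation row of Table 3 must be extended, since it now covers only completeness of data and participation on Instagram. If they become a secondary outcome, the Effectiveness and Maintenance rows need the addition.

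The cost is small in work, and data already collected remain usable. The real downside is that one WHO life-skill domain then has no primary measure in this study; this should be said in the Limitations section. An independent measure of creative or critical thinking could be considered for the later cluster-randomized trial.

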		**Interpersonal skills and empathy**					
			—	Questionnaire on resources in childhood and adolescence (FRKJ 8-16) [74]		α=.68-.89	
			—	Subscale “Social skills” of the Life Skills Ability Scale (LSAS) [73]		α=.82	
		Self-confidence and self-efficacy		Questionnaire on resources in childhood and adolescence (FRKJ 8-16) [74]		α=.68-.89	
		Dealing with emotions		Emotion regulation questionnaire [75]		α=.74-.76	
		**Dealing with stress**					α=.69-.88
			—	Stress- and Coping-Inventory (SCI)		—	
			—	Subscales “Physical symptoms” + “Coping strategies” [76]		—	
	**Social media–related skills**						
		Cyberbullying		European Cyberbullying Intervention Project Questionnaire (ECIPQ) [77]		α=.96	
		**Media-based empathy**					α=.80
			—	Media-Based Empathy (MBE)		—	
			—	Subscale “Cognitive Media Empathy with Real Persons” [78]		—	
		**Social media use**					
			—	Social media use time		—	
			—	Social media disorder scale-short form [79]		α=.81	
			—	Bergen social media addiction scale [80]		*r**_tt_*=.82	
		Smartphone use		Smartphone addiction scale [81]		α=.85	
**Secondary outcomes**							
	**Risk behavior**						
		**Substance use**					
			—	Alcohol Use Disorder Identification Test (AUDIT) [82]		α=.80	
			—	Cigarettes and cannabis - questions from the HBSC study [83]		—	
	**Health status**						
		Subjective state of health		Subjective state of health [84,85]		—	
		Well-being		World Health Organization-5 well-being-index [86]		α=.92	
		**Life satisfaction**					
			—	German version of the Satisfaction with Life Scale (SWLS) [87,88]		α=.87	
			—	Short scale for the assessment of general life satisfaction (L-1) [89]		*r**_tt_*=.67	
		Mental health: anxiety and depression		Hopkins Symptom Checklist-25 (HSCL-25) [90]		α=.94	
		School performance		School grades (German, English, and Math), grade point average, and change		—	
**Covariants**							
	**General**						
		**Acceptance and feasibility of the program**					—
			—	Self-generated items based on the Training Evaluation Inventory (TEI) [91]		—	
			—	Net-Promoter-Score		—	
		**Sociodemographic variables**					
			—	Gender, age, migration background, socioeconomic status: family affluence scale [92,93]		*r**_tt_*=.90	
			—	Subjective Socioeconomic Status scale (SSS-Scale) [94]		α=.70	

^a^Not applicable.

### Recruitment

This accessibility study will recruit participants via schools, youth centers, and therapeutic facilities across Germany. Adolescents from various school types (grammar, secondary, comprehensive, and independent) and socioeconomic backgrounds are targeted. Recruitment spans several federal states (Berlin, Mecklenburg-Western Pomerania, North Rhine-Westphalia, Saxony, Lower Saxony, and Thuringia), chosen for representativeness and synchronized holidays, encompassing both rural and urban areas. State school participation requires ethical approval and ministry or school board consent. Schools, youth centers, and therapeutic facilities are randomly selected within these states.

Recruitment will begin once approvals are obtained, with invitations issued in waves based on response rates. Teachers, youth workers, and therapists initially agreed to participate (Multimedia Appendix 1). Adolescents are then recruited through digital information events, which aim to build motivation to participate through highlighting the relevance of the programs’ content for their life stage (Multimedia Appendix 2). In addition to research findings on that, key adolescent concerns were identified in the pilot study. The use of Instagram minimizes participation effort and the recruitment in schools fosters group dynamics. Further, the program incentivizes engagement with rewards and ensures anonymity and confidentiality, creating a safe space for discussing sensible and at the same time interesting topics. Finally, together with their parents, adolescents agree to participate in the study.

To join the study, participants need an Instagram account, must be proficient in German, and must be aged 14-17 years. The recruitment goal includes 2 classes from grammar schools, 3 classes from secondary schools, and 1 class from an independent school per state, plus 20 adolescents from youth centers and therapeutic institutions in each state, accommodating additional participants if interested.

As we are taking an innovative approach, it is not clear how complete the recruitment will be. The sample size depends on adolescents who voluntarily want to participate. Since adolescents work on the program in their free time, it can be assumed that fewer will participate than in compulsory programs conducted in school. Recruitment will start in May 2023 and end as soon as the target criteria are met or the program starts in September.

### Data Collection

In this study, both qualitative and quantitative data are gathered to explore the RE-AIM framework’s dimensions, involving (1) documentation by the recruitment team and (2) personal-level outcomes via questionnaires. Figure 1 illustrates the study design with the recruitment phase and points of assessment.

To assess RE-AIM’s aspects of reach, acceptance, and implementation, data will be collected on the number of schools, youth centers, and therapeutic facilities contacted per state; their response rates; information events held; and consents after the event. The recruitment team will also document institutions’ responses.

Personal level characteristics outcomes, measuring reach, effectiveness, and maintenance, are gathered through web-based questionnaires in a preintervention, postintervention, and follow-up design. Participants and institutions receive unique codes for tracking. The institutional link aims for support through teachers or youth workers and therapists and thus comprehensive data collection by conducting the entire study, including data collection, within 1 school year. Schools optionally receive supplementary teaching materials for the leduin program content.

The following constructs are collected by means of questionnaires: primary outcomes (life skills [decision-making or goal setting, problem-solving, creative and critical thinking, communication, interpersonal skills and empathy, self-confidence and self-efficacy, managing emotions, and managing stress], and social media–related skills [media-based empathy, cyberbullying, smartphone, and addictive or disordered social media use]); secondary outcomes (health status [well-being, subjective health and mental health, and life satisfaction], risk behavior [substance use], and school performance); and covariants (acceptance and feasibility of the program and sociodemographic variables). Table 2 lists the survey instruments used to measure the constructs just described, including reliability.

For the web-based data collection of the participants’ personal data, we use the SoSci Survey platform with which we have an order data processing agreement for the leduin study that has been reviewed by the data protection officer of the University of Greifswald. This ensures the technical and organizational measures required for data security. The provider SoSci Survey works with SSL encryption (HTTPS) of the data when filling out the questionnaire and when retrieving the collected data. A secure SSL configuration (Qualys SSL Labs) secures the transmission of the data. The servers of the University of Greifswald are used to store the data. The data are secured by daily backup and are usually stored for 90 days (3 months).

The initial data collection in the pilot study proved successful due to teacher involvement. However, transferring responsibility for the subsequent data collection to the adolescents led to significant gaps in the data. To address this in the accessibility study, we will prioritize early emphasis on the importance of data collection and ensure consistent supervision of the adolescents to mitigate missing data issues.

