**Methods:**

The leduin program, developed through intervention mapping, applies behavior change techniques via social media for 9th and 10th graders. It is a 14-week spaced learning curriculum with daily sessions <5 minutes. Emphasizing the “reach” aspect of the reach, effectiveness, adoption, implementation, and maintenance (RE-AIM) model, the recruitment targets diverse educational settings across 6 German states, aiming for inclusivity. Recruitment will involve schools, youth centers, and therapeutic facilities. The study seeks at least 128 participants, a calculated minimum to detect medium-sized effects in the quasi-experimental design and explore varying engagement levels and program responses. Data collection includes preintervention, postintervention, and 6-month follow-up surveys, using multilevel regression, latent growth models, and qualitative analysis to extensively assess reach and gain first insights on effectiveness, acceptance, implementation, and maintenance. The study aims to reveal key factors influencing program participation and interaction; a detailed analysis of engagement patterns will reveal the effectiveness of the recruitment strategies and barriers to participation. Additionally, initial indications of the program’s impact on life skills, social media–related skills, health status, risk behaviors, and academic performance will be analyzed.

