## Methods

### Overview

The objectives of the accessibility study for the leduin program, grounded in the reach, effectiveness, adoption, implementation, and maintenance (RE-AIM) framework [71], primarily focus on evaluating the first dimension of the framework—“reach”—to identify effective strategies for engaging adolescents in digital life skills interventions on social media. This includes reaching a diverse demographic of 9th and 10th graders, encouraging participation, and ensuring sustained engagement. While also considering the remaining RE-AIM aspects—effectiveness, adoption, implementation, and maintenance—the study mainly seeks to understand the characteristics and engagement levels of participating adolescents and to identify what drives active or low engagement. This understanding is critical for refining recruitment strategies and enhancing the impact of social media–based health interventions for youth.

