Qualitative analyses of the recruitment process will be executed by conducting a qualitative content analysis [97] using the software MAXQDA (VERBI Software). This should provide information on the barriers to participation in the program and also identify the facilitators.

Table 3 summarizes the different dimensions of the RE-AIM framework, their operationalization, and corresponding statistical methods.

**Table 3 table3:** Dimensions of the reach, effectiveness, adoption, implementation, and maintenance (RE-AIM) framework, operationalization, and statistical methods to evaluate a social media–based life skills program (leduin).

Dimension	Operationalization	Statistical method
Reach	Dependent variables Initial interest Institutional level: number of institutions (schools, youth centers, and therapeutic facilities) contacted per federal state and positive responses Individual level: proportion of adolescents who agree to participate Qualitative process information of facilitators and carriers Independent variables from questionnaires Socioeconomic status, gender, age, mode of recruitment (school, youth center, and therapeutic facility), school type, well-being, life satisfaction, and mental health	Multilevel logistic regressions Qualitative content analysis
Effectiveness	Primary outcomes: Life skills and social media–related skills Secondary outcomes: mental health, well-being, risk behavior, school performance	Mixed-effect multilevel regression analysis with institutions (school, youth center, and therapeutic facility), classes, and individuals as evaluation levels and 3 measurement points (preintervention, postintervention, and follow-up) Latent growth models Logistic regressions
Acceptance	Dependent variables Willingness to participate: Number of information events Number of consents Individual engagement Independent variables from questionnaires Socioeconomic status, gender, age, mode of recruitment (school, youth center, and therapeutic facility), school type, well-being, life satisfaction, and mental health Qualitative process information of facilitators and carriers	Multilevel logistic regressions Qualitative content analysis

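### Reach is the stated primary focus, but only effectiveness outcomes are labelled primary: 12 constructs, against a sample size that covers one test

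*Protocol article*

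**What the plan says.** The Overview in Methods states that the objectives "primarily focus on evaluating the first dimension of the framework", and the Discussion repeats that reach is the main dimension.

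Data Collection then lists the "primary outcomes (life skills [decision-making or goal setting, problem-solving, creative and critical thinking, communication, interpersonal skills and empathy, self-confidence and self-efficacy", followed by managing emotions and managing stress, together with "social media–related skills [media-based empathy, cyberbullying, smartphone, and addictive or disordered social media use". Table 2 sets out the instruments under the same primary heading. One of them is home-made: "Self-generated items to test knowledge based on the developed program content". In Table 3 the effectiveness row carries "Primary outcomes: Life skills and social media–related skills", and the maintenance row repeats it. The reach row lists dependent variables at institutional and individual level without ranking any of them as primary.

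On size, the Effectiveness section says that "a power analysis indicates the need for 128 adolescent participants (power=0.8, α=.05". It describes this choice of effect size as "aligning with existing evidence of medium effect sizes in digital interventions (d=0.30 to 0.76". The Abstract presents the number as the study's minimum: "The study seeks at least 128 participants, a calculated minimum to detect medium-sized effects in the quasi-experimental design".

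**The concern.** The primary outcome should answer the primary question. Here the question is who can be reached and engaged, while the outcomes ranked primary ask whether skills change. A reader of the final report could not tell which result the study stands on.

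The primary set is also long and has no internal order, while the power statement is that of a single comparison. The study is meant to shape a later cluster-randomized trial. If a few of many nominally primary skill scores come out significant, the label gives them a weight that the stated power and α do not support.

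**Working it through.** **1. Labels against objective**

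| Place in the article | What it ranks first |
|---|---|
| Methods, Overview; Discussion | Reach |
| Table 2; Data Collection | Life skills and social media-related skills, called primary |
| Table 3, effectiveness and maintenance rows | The same skills, called primary |
| Table 3, reach row | Dependent variables named, none called primary |

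**2. How many primaries**

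Data Collection names 8 life-skill and 4 social media-related constructs: 12.

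Table 2, by score:
- goal setting, problem solving, knowledge items, communication: 4
- the childhood and adolescence resources questionnaire (used twice), social skills, emotion regulation, stress symptoms, coping: 6
- cyberbullying, media-based empathy: 2
- use time, two social media disorder or addiction scales, smartphone scale: 4

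The total is 16, or 15 if the two stress and coping subscales count as one entry.

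**3. Reproducing 128**

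Inputs from the article: power 0.8, α=.05, a medium effect. Assumed: d=0.5 (inside the cited range of 0.30 to 0.76), two-sided, equal groups.

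- Normal approximation: n per group = 2(1.960+0.842)²/0.5² = 62.8, so 63, or 126 in total.
- Two-sample t-test: 63.77, so 64 per group, **128 in total**. The figure reproduces.
- One-sided, it would be 51 per group (102).
- A paired test at d=0.5 would need 34. A paired test at d=0.25 also gives 128 (127.5 rounded up), but that effect lies below the cited range.

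On any of these readings the calculation is for one test.

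**4. What one-test planning means for the set**

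Assume, as the article does not say, that each primary is tested at .05 and that one significant result is read as success. With all nulls true and independent outcomes, the chance of at least one false positive is 1 − 0.95^m:
- m=12: 1 − 0.95^12 = 0.460
- m=15: 1 − 0.95^15 = 0.537
- m=16: 1 − 0.95^16 = 0.560

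With a common correlation r, the same quantity is 1 − ∫φ(u)[Φ((z−√r·u)/√(1−r)) − Φ((−z−√r·u)/√(1−r))]^m du, with z=1.96:

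| r | m=12 | m=16 |
|---|---|---|
| 0.3 | 0.397 | 0.476 |
| 0.5 | 0.319 | 0.374 |
| 0.7 | 0.232 | 0.264 |

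The article gives no correlations, so the range of r is an assumption.

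**5. The same gap seen as power**

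Under an illustrative Bonferroni split over 16 scores, α = .05/16 = .003125. Power at d=0.5 with 64 per group then falls from 0.80 to 0.43, and restoring 0.80 takes 118 per group (236). With two domain composites at α=.025 each, the total is 156.

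**The case against.** The strongest reply has four parts.

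- **Multiplicity rules belong in the analysis plan.** This stands. The absence of a Holm or false-discovery-rate rule from a condensed article is not a finding. The mismatch between objective and label is different: it is stated in the article, and an analysis plan would not remove it.
- **Effectiveness is described as preliminary.** True, and it lowers the stakes. It also argues against calling these scores primary. The Effectiveness section still speaks of testing a hypothesis and bases the sample size on it.
- **The labels may rank only the questionnaire battery,** since reach counts come from the recruitment team's records. This plausibly explains how the label arose. It does not cure it, because Table 3 covers all dimensions and still gives the primary rank to effectiveness and maintenance alone.
- **The stated hypothesis is narrower than the primary set.** It concerns social media skills and risk behavior, and risk behavior is labelled secondary. Only 6 primary scores fall under it: 1 − 0.95^6 = 0.265 if independent. This stands, and it shows again that labels and question do not line up.

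Three stronger readings are tempting and not supported.

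- **That the study will test 16 primaries at .05, so a chance success is close to a coin flip.** The only α is in the sample-size sentence, no success rule is stated, and subscales of one instrument and overlapping addiction scales may well be correlated.
- **That two later time points make 32 independent tests** (1 − 0.95^32 = 0.81). Repeated values from the same adolescents are not independent, and the plan models the three time points jointly.
- **That the 283 recruits restore the power lost to adjustment.** That number counts those who agreed to take part. Dropout is expected, and equal engagement groups and absence of clustering cannot be assumed.

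**Conclusion.** The point holds as a contradiction within the article. Reach is the primary focus, no reach variable is primary, and the 12 constructs that are primary (about 15 to 16 scores) belong to effectiveness and maintenance. The figure of 128 is correct for one two-sided two-group test at an assumed d=0.5; its power and α do not describe the primary set.

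The size of the error-rate problem is conditional. Under per-outcome testing at .05 and an any-one-counts reading, it runs from about 26% (16 scores, r=0.7) to 56% (16 scores, independent), with 46% for 12 independent constructs. These figures illustrate what the label invites; they are not error rates of a stated procedure.

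**What to change.** 1. Name the reach indicators as primary and report them with confidence intervals: the proportion of contacted institutions that took part in an information session, and the proportion of adolescents who agree to join after it. Both are defined in Statistical Methods. Table 3 describes the institutional measure as contacts and positive responses, so use one definition in both places.
2. In Table 2, Data Collection and the effectiveness and maintenance rows of Table 3, relabel life skills and social media-related skills as secondary or exploratory effectiveness outcomes.
3. In the Effectiveness section and the Abstract, say that power 0.8 at α=.05 refers to a single outcome.
4. False-discovery-rate control across the skill scores is optional if they are reported as exploratory.

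Record the change with its date and reason before outcome data are analysed, and carry it into the registration if that lists the same primaries. No new data are needed. The cost is that the skill results carry less confirmatory weight.
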